### Background

After introduction of the pneumococcal conjugate vaccine (PCV), invasive pneumococcal disease (IPD) and subsequent pneumococcal mortality has been reduced globally. Yet in 2015, pneumococcal infections are still estimated to cause 294,000 (range 192 –366,000) deaths in HIV-uninfected children under 5 years.(1) Some populations are at higher risk for IPD including young infants and specific ethnicities such as Aboriginal, Māori or Pacific people.(2, 3)

Several PCVs are commercially available and cover different serotypes (7-valent PCV (PCV7);10-valent PCV (PCV10) (Synflorix, GSK); 13-valent PCV (PCV13) (Prevenar 13, Pfizer)). In comparison with PCV10, PCV13 also includes the serotypes 3, 6A, and 19A. Previous studies comparing the impact of PCV10 and PCV13 programmes until 2017 have not found superiority for one of the two vaccines in the overall burden of pneumococcal disease.(4-6) The World Health Organization recommends that a switch in PCV programme should be made when epidemiology of IPD changes considerably.(6)

In the national immunisation programme of Australia PCV13 is used since 2011, whereas Aotearoa New Zealand (NZ) switched from PCV13 to PCV10 in 2017 (Appendix 1).(7, 8) When NZ switched to PCV10 in 2017 it was on the basis that immunogenicity studies suggested the inclusion of serotype 19F in PCV10 offers cross-protection for serotype 19A. Whether this cross-protection is sufficient to protect for infection by serotype 19A has been questioned.(9, 10) A recent NZ study showed that serotype 19A in IPD patients increased from 12% in 2017 to 21% in 2020 with overall IPD incidence remaining similar. Furthermore, half of the hospital admissions in children <5 years with IPD was due to serotype 19A, and penicillin-resistance in serotype 19A increased to 60%.(10) Recently, this trend of increasing serotype 19A infections has been noticed in several other countries around the world who use PCV10 on their infant immunisation schedule.(11-15)

Australia and New Zealand have had similar experiences in the COVID-19 pandemic with relatively low case numbers compared to other countries. As containment measures in the COVID-19 pandemic have shown to reduce IPD (16), Australia and New Zealand are relatively comparable in their IPD incidence. To our knowledge, no previous study has examined the influence of different

childhood immunisation programmes on IPD rate in Oceania. In this study, we aim to compare IPD incidence between Australia and New Zealand in 2017-2021, with a focus on young age, serotype 19A and ethnicity.

### Study objective

To compare IPD incidence and epidemiology between Australia and New Zealand in 2017-2021, with a focus on ethnicity, age and serotype 19A.

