## Impact

Epidemiological and surveillance studies such as our project, are crucial to evaluate vaccine strategies and to inform public health organizations on vaccine policies to improve health outcomes. This research will provide insight in differences of IPD and serotype rates and the influence of the PCV10 and PCV13 programmes. This study will provide us with an opportunity to compare PCV10 and PCV13 programmes based on real-life data. In addition, we will evaluate the IPD rate in specific ethnic groups who suffer from health inequalities. In these groups, it is even more essential to evaluate the effect of current vaccine strategies. Also, this project will provide essential data on the future decision of vaccine programmes in New Zealand and Australia.

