## Appendix 1 – Important changes in immunisation schedules for children in Australia and New Zealand over time

### Australia (7, 20)

|          |                                                                                         |                                                                                                                                                                                             |
|----------|-----------------------------------------------------------------------------------------|---------------------------------------------------------------------------------------------------------------------------------------------------------------------------------------------|
| 2001-Jun | Introduction PCV7 in Indigenous children and children with high-risk medical conditions | Indigenous : PCV 7 at 2, 4 and 6 months (PCV7), in high-incidence jurisdictions* PPV23 at 18-24 months, Medically high-risk : PCV7 at 2, 4, 6 and 12 months, PPV23 at 5 years |
| 2005-Jan | Universal 3 dose program PCV7                                                           | 2, 4 and 6 months (PCV7), with catch-up doses in children <2 years                                                                                                                          |
| 2011-Jul | PCV13 replaced PCV7                                                                     | Catch-up dose of PCV13 for children 12-35 months. Indigenous : in high-incidence jurisdictions PCV13 replaced PPV23 at 18-24 months.                                                 |
| 2018-Jul | PCV13 at different timings, change to 2+1                                               | PCV13 at 2, 4 and 12 months. Indigenous children in high-incidence jurisdictions*, and children at medically higher-risk : PCV 13 at 2, 4, 6 and 12 months (3+1)                     |

\*High-incidence jurisdictions: Northern Territory (NT), South Australia (SA), Queensland (QLD) and Western Australia (WA).

Indigenous: includes Aboriginal and Torres Strait Islander

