### New Zealand (8)

|          |                                                                                                               |                                                                                                                                   |
|----------|---------------------------------------------------------------------------------------------------------------|-----------------------------------------------------------------------------------------------------------------------------------|
| 2006     | PCV7 for high-risk children                                                                                   |                                                                                                                                   |
| 2008-Jun | Universal PCV7                                                                                                | PCV7 at 6 weeks, 3, 5 months and 15 months                                                                                        |
| 2011     | PCV10 replaced PCV7                                                                                           | For high-risk children : PCV13 replaced PCV7                                                                               |
| 2014     | PCV13 replaced PCV10                                                                                          |                                                                                                                                   |
| 2015     | PCV13 available for patients of any age with certain high-risk conditions                                     |                                                                                                                                   |
| 2017     | PCV10 replaced PCV13                                                                                          | PCV13 continues for high-risk individuals                                                                                         |
| 2020     | PCV10 dosing change: 2-dose primary schedule plus booster dose given at 6 weeks, 5 months and 12 months (2+1) | For high-risk infants : PCV13 remained at 3-dose schedule plus booster for high-risk infants (6 weeks, 3, 5 and 12 months) |

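### The 2017-2021 window suits a description of country rates, but with no pre-switch New Zealand to Australia ratio it cannot support the claimed comparison of PCV10 and PCV13 programmes

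*Protocol*

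**What the plan says.** The Study objective is "To compare IPD incidence and epidemiology between Australia and New Zealand in 2017-2021, with a focus on ethnicity, age and serotype 19A". Data analysis (Methods) compares overall rates and the serotype 19A proportion between the two countries over those years, then stratifies by ethnicity and age group and explores immunisation coverage. It states no contrast over time and no split by birth cohort or scheduled vaccine. Methods calls the study ecological and descriptive.

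The Impact section claims more: insight into the influence of the two programmes, data for future vaccine decisions, and "This study will provide us with an opportunity to compare PCV10 and PCV13 programmes based on real-life data".

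The programme history is in Background and Appendix 1:

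- **Australia:** "In the national immunisation programme of Australia PCV13 is used since 2011". In July 2018 the schedule changed ("PCV13 at different timings, change to 2+1").
- **New Zealand:** in 2014 "PCV13 replaced PCV10"; in 2017 "PCV10 replaced PCV13". Neither entry gives a month. The number of doses changed in 2020.

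**The concern.** A comparison of two countries in one period shows the sum of every difference between them. To attribute part of it to the vaccine programme, one needs to know the gap when both countries scheduled the same vaccine. The window opens in the switch year, so it contains no complete year before the switch.

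The protocol itself names other sources of difference: a higher burden in Māori and Pacific people, a case definition that differs on antigen testing (handled by exclusion), and extra doses for Indigenous Australian children. Its argument for comparability rests on similar pandemic experience, which says nothing about rates before 2017.

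Exposure in children also lags the schedule. Children aged 3 or 4 in 2018 started their course before the switch, so pooled New Zealand under-5 figures mix vaccine cohorts. That tends to dilute any true PCV10 versus PCV13 difference. At stake is whether a result offered for vaccine policy can bear that use.

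**Working it through.** **1. The gap that cannot be divided.** Sample size (Methods) gives 2019 rates per 100,000 of 8.4 (8.1-8.8) for Australia and 9.9 (9.1-10.8) for New Zealand.

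- Rate ratio: 9.9 / 8.4 = 1.18.
- Log-scale standard errors from the stated intervals: ln(8.8/8.1) / 3.92 = 0.0211 and ln(10.8/9.1) / 3.92 = 0.0437. Combined: √(0.0211² + 0.0437²) = 0.0485.
- Approximate 95% interval: 1.18 × exp(±1.96 × 0.0485) = 1.07 to 1.30.

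The protocol gives no pre-2017 ratio to set against the 1.18.

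**2. Model for New Zealand exposure.** Assumptions: uniform births, no migration, full coverage, no catch-up, high-risk exceptions ignored. Each child is assigned the vaccine scheduled at the first dose. Appendix 1 puts that dose at 6 weeks ("PCV7 at 6 weeks, 3, 5 months and 15 months", and again in the 2020 entry). The switches are placed at mid-2014 and mid-2017, then varied over the whole of each year. The birth-date cut-offs are 2014.5 − 6/52 = 2014.385 and 2017.5 − 6/52 = 2017.385.

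**3. Under-5s, 2017-2021** (5 ages × 5 years = 25 units of area)

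- Post-switch PCV10: a triangle with leg 2022 − 2017.385 = 4.615, so 4.615²/2 = 10.65, and 10.65/25 = 43% (range 34-52%).
- Earlier PCV10: leg 5 − (2017 − 2014.385) = 2.385, so 2.385²/2 = 2.84, and 2.84/25 = 11% (range 7-17%).
- PCV13: the remainder, 46% (range 31-59%).
- Post-switch PCV10 by year, 2017 to 2021: 4%, 22%, 42%, 62%, 82%.

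**4. Younger children, 2017-2021**

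- Under 1 year: time before post-switch cohorts is 0.385 × 1 + 1²/2 = 0.885 of 5, so post-switch PCV10 is 82% (72-92%).
- Under 2 years: 0.385 × 2 + 2²/2 = 2.77 of 10, so post-switch PCV10 is 72% (62-82%).

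**5. Which earlier period could serve as a PCV13 baseline?** This also needs the 2011 change from PCV7, taken as mid-2011.

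| New Zealand group and period | PCV13 | PCV10 | PCV7 |
|---|---|---|---|
| Under 5, 2014-2016 | 23% (15-32%) | 58% | 19% |
| Under 5, 2018-2021 | 43% (29-56%) | 52% post-switch, 5% earlier | 0% |
| Under 2, 2015-2016 | 76% (about 55-90%) | 24% | 0% |
| Under 2, 2018-2021 | 12% (about 5-22%) | 88% (about 78-95%) | 0% |

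For example, under-5 PCV13 in 2014-2016 is (2017 − 2014.385)²/2 = 3.42 of 15 = 23%. In under-2s the triangle outside the intended cohort has leg 1.385 and area 0.959. That is 0.959/4 = 24% in 2015-2016 and 0.959/8 = 12% in 2018-2021.

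A contrast of all under-5s would therefore give the PCV13 label to the period with less PCV13 exposure (23% against 43%). The under-2 contrast runs in the intended direction.

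**The case against.** The strongest defence is that the study calls itself descriptive and ecological, that its objective makes no causal claim, and that Appendix 1 discloses every switch. This stands for the objective. A reader might infer that the window is itself an error or that the protocol assumes all New Zealand children had PCV10. The documents support neither: describing 2017-2021 is legitimate, and no section says exposure was uniform. The defence does not cover the Impact section, which draws an inference about programmes.

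A second defence is that 2017 is nearly a pre-exposure year for the new programme. This is partly right. Post-switch PCV10 is only about 4% of under-5 time in 2017 (0-12% over possible switch dates), so to say the data hold no pre-switch information would be too strong. But 2017 is one transitional year, 38% of its under-5 time is earlier PCV10, and the protocol does not use it as a baseline.

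A third defence is that age-group analyses are already planned, and yearly display may be left to the SAP. Age strata do reduce the mixing, most of all in infants. Neither step supplies the missing pre-switch ratio, because the protocol fixes the study years.

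A reader might also infer that 2014-2016 is a ready-made baseline because both countries then scheduled PCV13 for infants. The table above shows that this fails for under-5s as a group. Finally, Ethical considerations describes the data as aggregated, so fine age-by-year cells, or comparable serotype data before 2017, cannot be taken for granted.

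**Conclusion.** The objective is sound. The programme inference in the Impact section is not supported, because a country-only contrast starting in the switch year cannot separate a standing gap from a programme effect. In 2019 the undivided excess is 18% (ratio 1.18, approximately 1.07 to 1.30).

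Mixed exposure adds to this in pooled under-5 figures, where only about 43% (34-52%) of New Zealand child-time is post-switch PCV10. It is a lesser problem in infants. The shares rest on the model assumptions above and on switch months that the protocol does not give. The identification problem does not depend on them.

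**What to change.** 1. Request at least 2015-2016 from the same surveillance and population sources, if comparable serotype data exist. Compare the change in New Zealand with the change in Australia, for 19A and total IPD, for example by a Poisson model with a country-by-period term and 2017 as a transition year.
2. Make this contrast mainly in under-2s. Do not use all under-5s in 2014-2016 as a PCV13 baseline. Split older children by scheduled vaccine only if the aggregated data give age by year.
3. Report rates by year, marking the 2018 (Australia) and 2020 (New Zealand) schedule changes, and do not rely on one pooled 2017-2021 figure.
4. If earlier data cannot be obtained, limit the Impact section to a description of country differences.

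**Cost.** A larger data request whose availability the protocol does not confirm, fewer cases in under-2s and so wider intervals, and one added model. The contrast would still assume that, apart from the switch, trends would have been parallel; the two schedule changes and the pandemic years fall in the later period and could disturb that. Item 4 costs only a change of wording.

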### Methods

**Study design:** This is an ecological study based on surveillance data from Australia and NZ

**Data collection:** We will collect IPD case notification data from national surveillance institutes (National Notifiable Diseases Surveillance System (NNDSS), EpiSurv) and merge those with census data that will be derived from Australian Bureau of Statistics and Statistics New Zealand. In NZ, all laboratories contribute to the surveillance system.

IPD is defined as a laboratory confirmed infections of *S. pneumoniae* if isolated from a normally sterile site or detected with nucleic acid testing from a sterile site. To be able to compare cases between Australia and NZ, cases detected from a newer generation *S. pneumoniae* antigen test on cerebrospinal fluid or pleural fluid will be excluded (NZ only). (17, 18)

National coverage of childhood immunisation data will be extracted from the National Immunisation registers in NZ and Australia. Fully immunised was defined as eligible children who have completed all of their age-appropriate immunisations by the time they turned the milestone age.

**Sample size:** This is a descriptive study so a power calculation is not required. Preliminary data show us that in 2019 overall IPD rates per 100,000 for Australia and New Zealand are on average 8.4 (95%CI 8.1-8.8), and 9.9 (95%CI 9.1-10.8), respectively. Therefore, this study will provide estimates for IPD rates with sufficient certainty.

**Data analysis:** First, we will compare overall IPD rates per 100,000 and the proportion of cases with serotype 19A between Australia and New Zealand between 2017-2021. Second, we will perform a stratified analysis for ethnicity: Indigenous (Aboriginal and Torres strait islander) versus non-Indigenous for Australia, and Māori and Pacific vs other for New Zealand. Next, we will analyse of IPD rates and serotype 19A rates in different age groups. Furthermore, we will explore whether differences in IPD rates can be explained by differences in national immunisation coverage for pneumococcal vaccinations. In a sensitivity analysis, we will repeat all the analyses only including non-Indigenous children in Australia because Indigenous children receive additional doses of PCV in certain regions (Appendix 1). Cases with missing indigenous status were counted as non-indigenous.

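### Overall, ethnicity and age-group rates are planned as separate one-way analyses without age standardisation, so age structure enters the all-age ethnic comparisons and, less so, the country comparison

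*Protocol*

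**What the plan says.** The data analysis paragraph of the protocol's Methods gives the analyses in order:

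- Country: "First, we will compare overall IPD rates per 100,000", together with the share of cases due to serotype 19A, Australia against New Zealand over 2017–2021.
- Ethnicity: "Second, we will perform a stratified analysis for ethnicity", with Indigenous against non-Indigenous people in Australia, and Māori and Pacific people against all others in New Zealand.
- Age: "Next, we will analyse of IPD rates and serotype 19A rates in different age groups". The age bands are not named.

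A sensitivity analysis then repeats everything with the Australian data restricted to non-Indigenous children. The reason given is their different vaccine schedule, not age. No step mentions standardisation or adjustment for age.

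For denominators, the data collection paragraph says the investigators will "merge those with census data that will be derived from Australian Bureau of Statistics and Statistics New Zealand". It names no population year.

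The study calls itself descriptive: "This is a descriptive study so a power calculation is not required". The Impact section nevertheless gives it a comparative purpose: "This study will provide us with an opportunity to compare PCV10 and PCV13 programmes based on real-life data".

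**The concern.** The protocol itself treats age and ethnicity as linked. The Background names young infants and certain ethnic groups as higher-risk populations, the objective makes both a focus, and the section on relevance to Māori health argues from the ethnic make-up of under-5 cases (39% Māori and 28% Pacific in 2020). Yet the ethnic comparison is planned for all ages together.

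If IPD risk varies with age and two ethnic groups differ in age structure, their all-age rates differ even when risk at every age is the same. A real excess can then be understated or overstated. This matters most for the groups whose burden the protocol says it is especially important to evaluate. The separate age step removes the problem for the countries, because each age band can be compared between them. It does not remove it for ethnic groups, because those age-band rates are not split by ethnicity.

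**Working it through.** **The protocol's own figures.** The sample size paragraph says the 2019 rates per 100,000 for Australia and New Zealand "are on average 8.4 (95%CI 8.1-8.8), and 9.9 (95%CI 9.1-10.8), respectively". No case counts or populations are given, so the rates cannot be rebuilt directly. The intervals can be checked with SE(log rate) = ln(upper/lower)/(2 × 1.96) and events = 1/SE².

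- Australia: ln(8.8/8.1)/3.92 = 0.0211, or about 2,240 cases.
- New Zealand: ln(10.8/9.1)/3.92 = 0.0437, or about 524 cases.
- Implied ratio, New Zealand to Australia: 9.9/8.4 = 1.18. SE = √(0.0211² + 0.0437²) = 0.0485, giving a 95% CI of 1.07 to 1.30.

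The stated intervals are consistent with Poisson counts. The ratio is not age-standardised as far as the protocol says.

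**Method.** Crude rate = Σ (population share in age band × rate in age band), with bands under 5, 5–64 and 65+. Both groups get the same age-specific rates, so the true ratio is 1.00 and any departure comes from age structure alone. All shares and rates below are assumptions; the protocol supplies none.

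**Ethnic comparison.** The older population is 6/77/17% throughout.

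| Assumed rates (<5 / 5–64 / 65+) | Younger population (%) | Crude rate, younger | Crude rate, older | Ratio |
|---|---|---|---|---|
| 8 / 5 / 30 | 11/83/6 | 0.88 + 4.15 + 1.80 = 6.83 | 0.48 + 3.85 + 5.10 = 9.43 | 0.72 |
| 15 / 6 / 25 | 10/84/6 | 1.50 + 5.04 + 1.50 = 8.04 | 0.90 + 4.62 + 4.25 = 9.77 | 0.82 |
| 20 / 5 / 15 | 11/83/6 | 2.20 + 4.15 + 0.90 = 7.25 | 1.20 + 3.85 + 2.55 = 7.60 | 0.95 |
| 30 / 5 / 10 | 10/84/6 | 3.00 + 4.20 + 0.60 = 7.80 | 1.80 + 3.85 + 1.70 = 7.35 | 1.06 |

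Rows 1 and 3 are the extremes of a grid with under-5 rates of 8 to 20, a 5–64 rate of 5 and 65+ rates of 15 to 30. The last row shows the direction reversing once under-5 rates dominate.

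**Country comparison.** Assume 6.3% under 5 in both countries, 16% aged 65+ in one and 14% to 17% in the other. The widest shift on the same grid is at rates 8/5/30:

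- 16% aged 65+: 0.504 + 3.885 + 4.800 = 9.189
- 14%: 0.504 + 3.985 + 4.200 = 8.689, ratio 0.95
- 17%: 0.504 + 3.835 + 5.100 = 9.439, ratio 1.03

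Taking the largest shift in the unfavourable direction (9.189/8.689 = 1.058), the implied 1.18 becomes 1.18/1.058 = 1.11.

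**The case against.** The strongest objection is that this reads silence as a statement. The protocol never uses the words crude or rate ratio, and a statistical analysis plan, not seen here, could specify standardisation. That stands as far as the choice of standard population and the age bands go. It does not dispose of the point. The protocol fixes the sequence of analyses, and its ethics section says the surveillance data will be aggregated. If the tables requested are one-way, an unseen plan cannot recover the crossing afterwards, and the timeline puts the analysis in the month after ethics approval.

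Second, an unstandardised all-age rate is a legitimate measure of burden in a descriptive study. That is true and is a reason to keep it, but the stated aim of comparing vaccine programmes calls for a standardised rate beside it.

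Third, age is partly handled. Age-group rates largely free the country comparison of age structure. The sensitivity analysis, read literally, also produces age-group rates for non-Indigenous children in Australia. It plans no matching Indigenous rates and nothing comparable for Māori or Pacific people, so the ethnic comparisons remain exposed.

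Fourth, the direction of the ethnic bias is not known from the documents. This stands in full: it cannot be said without qualification that the planned comparison understates the excess in the younger group.

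**Conclusion.** The point holds, chiefly for the ethnic comparisons. Followed as written, the plan mixes age structure into the all-age contrasts of Indigenous with non-Indigenous people and of Māori and Pacific people with others. Under the assumed age mixes and rates, the distortion runs from about 28% downward to about 6% upward. These figures illustrate the possible size; they are not estimates for these populations.

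Two stronger conclusions might be inferred, and the documents support neither.

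- That age structure undermines the country comparison. The contrast giving 0.82 sets a population with 6% aged 65+ against one with 17%, and nothing in the protocol suggests such a gap between the two countries. With the closer age structures assumed above, the shift is about 5% or less and would not by itself account for 1.18.
- That the rates rest on fixed census counts that drift over 2017–2021. Growth of 1–2% a year with a denominator one to four years out of date would overstate an annual rate by about 1% to 8% (1.02⁴ = 1.08), and much of that would cancel between countries if both were similarly affected. But the protocol does not say that a single census count is used. Its wording is loose, which warrants a clarification and no more.

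**What to change.** - Before extraction, request case counts and denominators cross-tabulated by age group, ethnicity and year for both countries, and name the age bands.
- Report directly age-standardised rates, using one common standard population, beside the crude rates for both the country and the ethnic comparisons.
- Report ethnicity-specific rates within age groups, including under 5 years.
- For clarity, replace the reference to census data with annual population estimates matched to each case year.

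The cost is more tabulation and some sparse cells, particularly for smaller ethnic groups in single years; pooling years within age bands is one way to handle these. Both statistics agencies are already named and an age-group analysis is already planned, so no new data source is proposed. The protocol does not show that the surveillance systems will release the full cross-tabulation, so this should be confirmed when the data are requested.

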## Relevance to Māori health

Indigenous populations in New Zealand and Australia, along with Pacific peoples have a much higher burden of disease for IPD.(2, 3, 19) For instance, two-thirds of all IPD cases in 2020 among children aged <5 years were children of Māori (39%) or Pacific (28%) ethnicity.(10) Australia provides two additional PCV23 (Pneumovax 23) doses for Aboriginal and Torres Strait Islander children, from 4 years of age.(7) New Zealand's programme, however, does not have additional doses for Māori or Pacific people. In this study, we will evaluate the IPD rate in specific ethnic groups including Māori as it is even more essential to evaluate the effect of current vaccine strategies in groups at higher-risk for IPD. This study has the potential to guide future decisions regarding vaccine strategies for Māori.

Māori consultation will be requested following the procedure by the Otago university.

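### The lead Australia-New Zealand rate comparison pools ethnic groups with very different IPD risk, so it cannot by itself support a PCV10 v PCV13 reading; a matched lower-risk contrast should be stated

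*Protocol*

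**What the plan says.** Protocol, Methods, Data analysis, sets out the comparisons in order.

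- First: "we will compare overall IPD rates per 100,000 and the proportion of cases with serotype 19A between Australia and New Zealand between 2017-2021". No ethnic restriction or adjustment is stated.
- Second, a stratified analysis for ethnicity, with the strata given as "Indigenous (Aboriginal and Torres strait islander) versus non-Indigenous for Australia, and Māori and Pacific vs other for New Zealand". Each contrast lies inside one country.
- Next, IPD and 19A rates by age group, with no ethnic split stated.
- Finally, a sensitivity analysis that will "repeat all the analyses only including non-Indigenous children in Australia because Indigenous children receive additional doses of PCV in certain regions". No matching restriction is stated for New Zealand.

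Under Relevance to Māori health, the Protocol says Indigenous and Pacific peoples have a much higher IPD burden and gives one figure: "two-thirds of all IPD cases in 2020 among children aged <5 years were children of Māori (39%) or Pacific (28%) ethnicity". Background also names Aboriginal, Māori and Pacific people as being at higher risk. Under Impact it says: "This study will provide us with an opportunity to compare PCV10 and PCV13 programmes based on real-life data".

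**The concern.** A pooled national rate is an average of group rates weighted by population share. Where one group has a much higher rate, a country in which that group is a larger part of the population has a higher pooled rate, whatever vaccine it uses. The Protocol itself reports the difference in burden, but the contrast it puts first leaves composition in.

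What is at stake is the use made of the result. The Impact section presents the study as a comparison of two vaccine programmes that will inform vaccine policy. A pooled New Zealand excess could be read as a PCV10 disadvantage when part or all of it reflects who lives in each country. The stratum rates that would help to separate the two will be computed, but the text does not say that they will be set against each other across countries.

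**Working it through.** **Inputs from the Protocol**
- 2019 all-age rates: "overall IPD rates per 100,000 for Australia and New Zealand are on average 8.4 (95%CI 8.1-8.8), and 9.9 (95%CI 9.1-10.8), respectively".
- Māori and Pacific share of New Zealand under-5 cases in 2020: 39% + 28% = 67%, which leaves 33% other.

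**Inputs assumed, because the documents give none**
- Under 5: Māori and Pacific population share in New Zealand m = 0.30-0.50; Indigenous share in Australia a = 0.03-0.07.
- All ages: higher-risk share pNZ = 0.15-0.30 and pAU = 0.03-0.04.
- Equal rates in both countries for the higher-risk groups, and likewise for the lower-risk groups, so that the true within-stratum ratio is 1.

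**Step 1: the plan's own figures.** The Protocol states no ratio. Its rates give 9.9/8.4 = 1.18. Standard errors of the log rates from the interval widths are ln(8.8/8.1)/3.92 = 0.021 and ln(10.8/9.1)/3.92 = 0.044, combined 0.049. The 95% interval for the ratio is about 1.07 to 1.30. Case counts and denominators are not given, so the printed intervals cannot be recomputed directly.

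**Step 2: formula.** With a lower-risk rate λ and a higher-risk rate Rλ in both countries, a pooled rate is λ[1 + p(R-1)]. The New Zealand:Australia ratio from mix alone is therefore [1 + pNZ(R-1)] / [1 + pAU(R-1)].

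**Step 3: under 5.** The 67% case share fixes R for each assumed m: R = (0.67/m) / (0.33/(1-m)).

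| m | R | Numerator 1 + m(R-1) | Ratio, a = 0.03 | Ratio, a = 0.07 |
|---|---|---|---|---|
| 0.30 | 4.74 | 2.12 | 2.12/1.11 = 1.91 | 2.12/1.26 = 1.68 |
| 0.50 | 2.03 | 1.52 | 1.52/1.03 = 1.47 | 1.52/1.07 = 1.41 |

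Mix alone gives about 1.4 to 1.9.

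**Step 4: all ages.** Solve the formula for the R at which mix alone yields the observed 1.1786: R = 1 + 0.1786/(pNZ - 1.1786 × pAU).
- pNZ = 0.15, pAU = 0.04: 1 + 0.1786/0.1029 = 2.74.
- pNZ = 0.30, pAU = 0.03: 1 + 0.1786/0.2646 = 1.67.

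The 2019 ratio therefore needs no within-stratum difference once R is about 1.7 to 2.7. Steps 3 and 4 concern different populations, so the under-5 range should not be set against the all-age 1.18.

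**Step 5: the sensitivity analysis as worded.** If Indigenous children are dropped in Australia only, the denominator in Step 3 becomes 1. The mix-only ratio then equals the numerator, 1.52 to 2.12, against 1.41 to 1.91 before. One-sided restriction widens the imbalance under these assumptions.

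**Step 6: the 19A proportion.** Mix would move it only if the 19A share of cases differs by ethnicity. The documents give no such figure, so nothing can be computed.

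**The case against.** The strongest reply concerns the wording. The objective is a comparison between the two countries with a focus on ethnicity. A stratified analysis that follows a country comparison may mean that comparison repeated by stratum, with the listed groups only defining strata that must be coded differently in each country. Repeating all analyses with Australia restricted also fits a cross-country reading. A reader might infer that the authors have ruled out any contrast of like strata. The text does not go that far: it leaves that contrast unstated. What stands against the reply is that the contrasts actually worded are "Indigenous (Aboriginal and Torres strait islander) versus non-Indigenous for Australia" and "Māori and Pacific vs other for New Zealand", and that the sensitivity restriction is one-sided.

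A second reply is that the study calls itself descriptive and ecological, and that calculation detail belongs in an analysis plan. That is fair for model choice or standardisation method. But the Protocol itself selects and orders the comparisons, and its Impact section attaches a programme reading to them.

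A third reply is that every population share above is assumed and that the 67% comes from one year. This stands in full. The calculation shows that mix can matter, not how much it does.

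**Conclusion.** The concern holds as a matter of interpretation: the pooled rate ratio contains any difference in ethnic composition and cannot by itself carry the PCV10 v PCV13 comparison. The possible size is a mix-only ratio of about 1.4-1.9 under 5, or the whole of the 2019 all-age 1.18 at a higher-risk rate ratio of about 1.7-2.7. Both rest on the assumed shares and on equal group rates in the two countries.

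Three stronger conclusions are tempting but unsupported.
- A reader might infer that the 2019 excess is compositional. It could be, but the documents give neither the shares nor the group rates needed to show it.
- A reader might infer that adjustment would reverse the direction of the under-5 difference. No crude under-5 country ratio is given, so this cannot be said.
- A reader might infer that the 19A proportion is biased too. Neither the presence nor the direction of such a bias can be shown.

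The upward push on the New Zealand ratio also requires New Zealand to have the larger higher-risk share. That is assumed here and not stated in the documents.

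**What to change.** In Methods, Data analysis:
- State that the ethnicity-stratified analysis includes the between-country rate contrast of New Zealand 'other' v Australian non-Indigenous, for IPD and 19A rates and in the same age groups.
- Present it beside the pooled ratio wherever PCV10 and PCV13 programmes are interpreted.
- Apply the sensitivity restriction to the corresponding New Zealand stratum as well.
- Report the higher-risk strata side by side as descriptive only. Their schedules differ: the Protocol describes additional doses for Indigenous children in Australia and none for Māori or Pacific people. Cases with missing Indigenous status are also counted as non-Indigenous.

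The cost is protocol wording and a few ratios from rates already planned, with no new data. The New Zealand 'other' stratum holds about one third of under-5 cases (2020 figure), so the standard error of its log rate is about 1/√0.33 = 1.7 times that of the pooled New Zealand under-5 rate. The two lower-risk strata are similar but not identical populations, and the rule for missing status affects the Australian one too. The matched contrast therefore reduces the composition problem without making the country ratio a pure programme effect.
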